### Randomization procedures and methods

Block randomization will be used following the procedure described in Altman and Bland [29]. It is desirable to have the number of participants allocated to each treatment condition similar at all times, in order to fill the treatment groups at approximately equal rates. The random number sequence will be generated by CI [name], in the following manner. Using blocks of four, there are only six possible ways of combining treatments A and B. Therefore for each sequence of four eligible families, both treatment conditions will be allocated twice. Six blocks will be generated. Using the website http://www.random.org, a random number series will be generated using numbers in the range of 1 to 6. A number will be allocated to each block. A second random number sequence will be generated for the allocation of blocks again. Blocks will then be arranged by going down each column until 200 conditions are allocated for Melbourne referrals, and a further 60 allocated for Geelong referrals. Finally a coin will be tossed where PAST = A and BEST-MOOD = B for heads, or PAST = B and BEST-MOOD = A for tails.

Sequentially numbered, opaque, sealed envelopes will be used to store the allocations, kept with the trial manager. Those allocating to treatment condition (intake workers) will be blinded to the randomization sequence and the overall study hypotheses.

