### Sample size and power

The trial aims to recruit a total of *n* = 160 participants. Based on pilot work and previously conducted clinical trials of family-based interventions compared to treatment-as-usual conditions, it has been estimated that it is possible to generate an effect size of *d* = 0.63 in reduction of mental health symptoms, which is equivalent to 14% increase in the odds of remission [45]. Out pilot data also indicates that treatment type by time interaction is able to produce up to 50% remission in depression diagnosis, over and above treatment type. With an alpha of 0.05 and power level of 0.90 for two-tailed tests, intraclass correlation coefficient (ICC) of 0.17 for within therapy group variation (estimated from our pilot data), and estimated 10% of variation in the main outcome accounted for by other variables in the model (treatment arm, time, parental socioeconomic status), the minimum sample size required equates to *n* = 57 per treatment arm. Based on pilot studies, an attrition rate of 20 to 25% is anticipated. Therefore, a minimum of 80 participants into each of the two treatment conditions will be recruited. Comparisons will be undertaken between those who drop out and those who are retained in order to assess for attrition bias.

With respect to our secondary hypotheses, anticipated final sample size of 114 individuals, will also allow us to detect small effect size (d = 0.23) for the treatment arm by time interaction for continuous outcomes, with 90% power and alpha level of 0.05, assuming ICC of 0.20 for within-person (between-assessment) and ICC of 0.07 for within therapy group variation (estimated from our pilot data).

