### Statistical analysis plan

Repeated measures binomial data will be analyzed over three time points using a binary logistic regression within the Generalized Linear Mixed Model (GLMM). The model will be fitted in STATA (xtmelogit). For any continuous-scale data we will use a linear mixed model approach in STATA. For both types of data we will explore variance-covariance structures for the evaluations within an individual. Clinical significance and an index of reliable change will be calculated for each measure using the criteria of Jacobson and Truax [46]. Findings will be analyzed in terms of standardized mean differences and effect sizes achieved will be compared to existing high quality trials to determine relative efficacy of this intervention. Multivariable multilevel models will also explore other covariates on the relationship between treatment arm and study outcomes, with a view to improving the intervention and specifying its ideal target population. Data will be stored in a locked cabinet, and a password protected computer file will contain de-identified (coded) data. A proportion of the data will be double-entered, and range checks will be performed for accuracy checking. Intention-to-treat analysis will be used with the last observation carried forward as a conservative estimate of outcome when data are missing at follow-up.

In addition, analysis of qualitative data from the transcribed interviews of participants who did not take up the option of treatment following intake/assessment, discontinued treatment, or completed treatment will be undertaken. Thematic analysis of participants’ accounts of their experience of the intake/assessment process and reasons for either engaging with or distancing themselves from the treatment offered will be undertaken. Meanings participants assign to the process will also be extracted from the data. Analysis of the data relevant to the phenomena of interest will assist in the identification of barriers to engagement and change for families.

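### The primary model as described omits the region used for allocation and baseline depression severity; prespecifying both costs almost nothing, and any gain in power comes from severity

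*Protocol article*

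**What the plan says.** **Allocation.** Randomization procedures and methods uses blocks of four and runs them "until 200 conditions are allocated for Melbourne referrals, and a further 60 allocated for Geelong referrals". The word stratified is not used, but balance is forced separately in each region.

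**Model terms.** Sample size and power refers to an "estimated 10% of variation in the main outcome accounted for by other variables in the model (treatment arm, time, parental socioeconomic status"). The Abstract adds a time-by-treatment effect and random effects for group and family characteristics. Statistical analysis plan gives the primary model as a mixed logistic regression over three time points, without a covariate list, and then says: "Multivariable multilevel models will also explore other covariates on the relationship between treatment arm and study outcomes".

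**Baseline data.** The sections on outcome measures and on parent, youth and sibling questionnaires collect the SMFQ by youth and parent report at all three time points. Table 1 excludes a young person who is unwilling to complete the baseline questionnaire. Inclusion criteria require a current major, minor or dysthymic disorder at entry.

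**The concern.** A factor that determined allocation normally belongs in the analysis, so that the analysis reflects the design. Here the one baseline covariate the article names, parental socioeconomic status, played no part in allocation, while region did and is not named.

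The second gap is easier to miss. A model over three time points that includes baseline looks as though it already adjusts for the starting level. For a continuous score it does use that level. For remission it does not: nobody is in remission at T1, so that wave cannot separate a mildly affected youth from a severely affected one. If severity predicts remission, the primary comparison gives up power that data already in hand could supply.

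**Working it through.** **1. Terms set side by side.**

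| Variable | Used in allocation | Collected at baseline | Named as a primary-model term |
|---|---|---|---|
| Region (Melbourne/Geelong) | yes | yes | no |
| Youth-reported SMFQ | no | yes | no |
| Diagnosis category | no (entry only) | yes | no |
| Parental socioeconomic status | no | not stated; implied by the model | yes |

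The two lists hold 200 and 60 places, both multiples of four, so each closes on a complete block. Geelong's share of the lists is 60/260 = 23%.

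**2. The plan's own sample size.** Inputs from Sample size and power: "With an alpha of 0.05 and power level of 0.90 for two-tailed tests"; "effect size of *d* = 0.63 in reduction of mental health symptoms"; "intraclass correlation coefficient (ICC) of 0.17 for within therapy group variation"; and the 10% of variation quoted above.
- Unclustered: 2 × ((1.960 + 1.282)/0.63)² = 52.9, so 53 per arm.
- With the 10% reduction: 52.9 × 0.90 = 47.7, so 48.
- With clustering: 47.7 × (1 + (m − 1) × 0.17), where m is the number per therapy group. m = 2 gives 56; m = 8 gives 105.

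The stated 57 cannot be reproduced because m is not given. It is used below only as the size of the simulated arms.

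**3. Value of adjustment.** Simulated: a single follow-up time, ordinary logistic regression, 57 per arm, 3,000 trials per row, and a two-sided Wald test at 5%. Assumed:
- control log-odds of remission of −0.6 in Melbourne, a probability of 1/(1 + e^0.6) = 35%;
- an odds ratio of 3.13, which is d = 0.63 converted by exp(0.63 × π/√3), or 2.5;
- a regional log-odds difference of 0.3 or 0.7, with roughly the list shares;
- a standardised severity score with log-odds 0 to 1.0 per SD.

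The article equates its effect size with a 14% rise in the odds of remission, which does not match this conversion. That is a separate matter and is not used here.

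| Odds ratio | Severity, log-odds per SD | Region, log-odds | Power, unadjusted | Plus region | Plus region and severity |
|---|---|---|---|---|---|
| 2.5 | 0 | 0.3 | 68.7% | 68.7% | 69.1% |
| 2.5 | 0.4 | 0.3 | 65.0% | 65.1% | 67.1% |
| 2.5 | 0.7 | 0.3 | 59.2% | 59.3% | 63.4% |
| 2.5 | 1.0 | 0.3 | 52.6% | 52.6% | 59.8% |
| 2.5 | 0 | 0.7 | 65.1% | 65.3% | 66.1% |
| 3.13 | 0 | 0.3 | 84.8% | 84.8% | 85.0% |
| 3.13 | 0.4 | 0.3 | 83.4% | 83.5% | 85.4% |
| 3.13 | 0.7 | 0.3 | 75.4% | 75.4% | 80.1% |
| 3.13 | 1.0 | 0.3 | 70.6% | 70.6% | 78.4% |
| 3.13 | 0 | 0.7 | 84.2% | 84.3% | 84.5% |

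Region alone moves power by at most 0.2 points. Adding severity gives 2.0 to 2.1 points at 0.4 per SD, 4.2 to 4.7 at 0.7, 7.2 to 7.8 at 1.0, and 0.2 to 1.0 when severity has no effect. Each power figure has a simulation standard error of at most √(0.25/3000) = 0.9 points; the models in a row were fitted to the same data sets, so their differences are more precise than that.

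**4. Where the gain comes from.** At an odds ratio of 3.13 and severity 0.7, the mean standard error of the log odds ratio rises from 0.392 unadjusted to 0.426 with both covariates. Power still rises because the unadjusted estimate is pulled toward no effect, and adjustment restores more than the standard error costs.

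**The case against.** **This belongs in the analysis plan, and only a condensed article is shown.** A complete list of fixed effects is commonly left to that plan, and the list quoted here explains an input to the power calculation. It is also incomplete, since the Abstract adds terms. This stands in part: an unseen analysis plan may already name region and severity, and then only the article's wording needs aligning. But the article is not silent. It names a covariate for the model, omits the allocation factor, and places other covariates in exploratory models.

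**Region hardly matters.** This stands as to power. Region is there for consistency with the design.

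**The simulation is not the planned model.** It has no therapy-group clustering and no repeated measures. Random effects for group and person would absorb some of the unexplained variation, so the figures do not carry over exactly. This stands as to size.

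**Stronger readings that the documents do not support:**
- *That the omission makes standard errors needlessly large, so adjustment buys precision.* On the log-odds scale the standard error rises with adjustment.
- *That the trial is already short of its stated power.* This turns on the therapy-group size, which is not given.
- *That SMFQ and diagnosis are the strongest predictors of remission.* No figure for prognostic strength appears.
- *That covariates for the primary result will be picked after seeing the data.* The exploratory models are described as additional, and as serving to refine the intervention and its target population.
- *That each continuous outcome also needs its own baseline as a covariate.* T1 is one of the modelled time points, so the baseline value is already used; adding it as a covariate while T1 stays in the outcome vector would use it twice.

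**Conclusion.** The point holds as a modest improvement and does not invalidate the analysis. The article describes separate allocation by region and a baseline severity score, names neither among the primary-model terms, and uses a binary outcome that cannot adjust for severity at T1. The benefit of region is agreement between design and analysis, with power almost unchanged. The benefit of severity ranges from about none to 7 or 8 points, depending on a prognostic strength assumed between 0 and 1.0 log-odds per SD, at 57 per arm, and in a simpler model than the one planned. The facts about allocation and named terms are firm; the size of the gain is not.

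**What to change.** Add one sentence to the analysis plan, or align the article with it if the terms are already there. The primary mixed logistic model should include region (Melbourne/Geelong) and baseline youth-reported SMFQ as prespecified fixed effects, with baseline diagnosis category (major, minor, dysthymia) as an optional third. Add region to the linear mixed models for continuous outcomes, and do not add the outcome's own baseline while T1 remains in the outcome vector. Keep the remaining covariates exploratory.

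The cost is two parameters in the primary model, or four with the three-category diagnosis, and one in each continuous-outcome model. No new data are needed: region is known at allocation, and the baseline questionnaire is a condition of entry.

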### Planned interventions

#### Behavior exchange systems training - mood (BEST MOOD)

BEST MOOD is a fully manualized treatment that has been developed based on family-systems theory. It consists of an eight-week, professionally-led group program designed to assist concerned parents to effectively initiate family changes to reduce youth depression. The active components of the BEST MOOD program include: mental health literacy; clarification of roles within the family; clarification of family goals to reinforce parental vision and leadership; skills in family communication, positive reinforcement and boundary setting; encouraging parent/guardian self-care; stress reduction techniques, encouragement of family connectedness; and family homework tasks related to these treatment components. The parent/s initially receive four, two-hour sessions of weekly intervention, after which the adolescent (12 to 18) and siblings (aged 12 years of age and over) are invited to also attend with their parents and complete four additional, two-hour sessions of a multi-family weekly intervention. During these last four sessions there are whole group activities, and also activities in smaller groups of parents and adolescents separately.

### Parenting Adolescents Support Training (PAST)

The PAST intervention will act as the treatment-as-usual control condition in this trial. Parents will attend a professionally facilitated parenting group which uses supportive counselling techniques. The PAST intervention runs for eight, weekly two-hour sessions. Youth and siblings (aged 12 and over) are invited to join in the fifth week. This intervention has been manualized for the purpose of this study. The content of PAST has been designed to equate with standard practices in currently available services in Australia, where if any service is offered, it is likely to consist of a parent support group. The development of this intervention was guided by the current protocols for the family mental health support services in Victoria, Australia. The PAST intervention offers: (a) supportive counselling to assist parents to articulate and identify concerns and (b) psycho-education to increase parents’ knowledge about youth mental health problems. The main content of the PAST group is support and the opportunity to share experiences and ideas as well as receiving contact with a mental health professional.

### Assessments and outcome measures

The following measures will be administered to assess the previously described study hypotheses across three time points during the trial: enrollment in the trial (T1), completion of treatment (T2), and three months post-treatment completion (T3). To maximize the clinical validity of the outcome evaluations, these assessments will involve both clinician administered and self-report measures. These measures have been chosen based on piloting in previous trials and in terms of minimizing participant burden while maximizing sensitivity to clinical change across key domains.

### Screening measures

#### Demographics

Demographic and clinical information will be collected from parent(s)/caregiver(s) and youth, including presenting problems, mental health history and treatment, family structure, and current psychotropic medications.

#### Youth depressive disorders

The Structured Clinical Interview for *DSM-IV Childhood Diagnoses* (KID-SCID) [28] is a semi-structured instrument designed to generate childhood *Diagnostic and Statistical Manual of Mental Disorders Fourth Edition DSM-IV*[30] diagnoses for clinical research studies. This instrument is modeled on the extensively used adult version (SCID). The modular nature of the KID-SCID permits users to select modules relevant to their research. For the purpose of this trial, modules were selected to enable the differential diagnosis of major depressive disorder, minor depressive disorder and dysthymic disorder. The selected modules were then tailored for use, such that two versions were created: one for completion with the young person, and a brief screening version for completion with a parent/caregiver. The KID-SCID modules will be conducted via telephone with young people, to determine eligibility and to assess the primary study hypothesis.

Modules of the KID-SCID selected for use with young people in this study as follows: Current Major Depressive Episode B1; Current Manic Episode B6; Hypomanic Episode B10; Dysthymia B14; Mood Disorder Due to a General Medical Condition B18; Substance Induced Mood Disorder B20. Modules B6, B10 and B18 and B20 were included as the differential diagnosis of major depressive, minor depressive and dysthymic disorders requires information elicited in the completion of these modules. On the recommendation of KID-SCID developer [name], the research team also used the following modules to the KID-SCID in the current trial: Past Major Depressive Episode, Past Manic Episode, Past Hypomanic Episode, and Major Depressive Disorder E4. These additional modules enable Current Mood Disorder Differential Diagnosis Module E to be completed. Mania, Hypomania and Bipolar Episodes and Disorders were only assessed to the extent that they could be ruled out for the purpose of accurate differential diagnosis of the depressive disorders.

Modules from the KID-SCID were also selected to form a proxy measure of major and minor depressive episodes or dysthymia for adolescents based on parent report. This will be conducted with the parent with regard to their adolescent. Included are: Current Major or Minor Depressive Episode; Dysthymia - single item; Mood Disorder Due to a General Medical Condition B18; Substance Induced Mood Disorder B20. The convergence of diagnosis via this parent proxy version of the KID-SCID and the adolescent administered KID-SCID will be assessed as part of the trial.

#### Youth psychotic symptoms

For differential diagnosis, psychosis will be screened using selected items of the Psychosis-Like Symptoms Interview PLIKS; [24]. Positive screens will be further assessed by a senior clinical psychologist to determine if the participant should be excluded on the basis of meeting diagnostic criteria.

### Parent, youth and sibling questionnaires

Participating families will also complete a set of questionnaires at baseline, post-group and at three month follow-up, in order to assess the secondary study hypotheses. Group attending parents/caregivers, the young person with depression symptoms, and their siblings aged 12 and over residing in the family home will all be invited to complete a set of questionnaires, as follows.

#### Youth and sibling mental health

*The Strengths and Difficulties Questionnaire (SDQ)* consists of 25 items [31]. The questionnaire will be reported by the parent about the youth with depressive symptoms, and the youth and siblings about themselves. The items load onto five subscales relating to youth mental health, including emotional symptoms, conduct problems, hyperactivity/inattention, peer relationship problems and prosocial behavior. *The Short Mood and Feelings Questionnaire (SMFQ)* consists of 13 items, which are administered to identify depressive symptoms amongst youth. The SMFQ is based on the 34-item version. Higher scores reflect more depressive symptoms [32]. The questionnaire will be administered to the parents (reporting about youth), youth (self-report), and siblings (self-report). A considerable amount of research indicates that the SMFQ and SDQ have good reliability and validity [33-35]. *The Alcohol Use Disorders Identification Test (AUDIT)* will be administered to identify recent problem alcohol drinking behavior [36]. The AUDIT has shown sound psychometric properties in prior research [37-39]. *The Depressive Experiences Questionnaire for Adolescents (DEQ-A shortened)* is a 20-item questionnaire is designed to assess youth depressive symptoms, and was developed from the 66-item DEQ for adults [40]. Items were identified from the DEQ according to their loading onto the three subscales; self-criticism, dependency and efficacy [41]. Adequate internal consistency has also been demonstrated (DEQ-A shortened self-criticism subscale alpha = 0.65, DEQ-A shortened dependency subscale alpha = 0.70, DEQ-A shortened efficacy subscale alpha not reported) [41].

#### Parent mental health

*The Depression Anxiety Stress Scales-21 (DASS-21)* is a 21-item measure which reflects three subscales including depressive symptoms (7 items), anxiety symptoms (7 items) and stress/tension items (7 items) experienced over the previous week (9), and will be self-reported by parents. The items from the original 42-item measure, which loaded most highly onto the subscales, were selected and reflect those included in the DASS-21 [42]. Comparable convergent validity has been found with other scales designed to measure depression, anxiety and stress or tension (that is, Beck Anxiety Inventory (BAI) and DASS-21 Anxiety subscale *r* = 0.85, Beck Depression Inventory and DASS-21 Depression subscale *r* = 0.79, BAI and DASS-21 stress/tension subscale *r* = 0.70) [43]. Good internal reliability has also been shown [43].

#### Familial relationships

*The Kansas Family Life Satisfaction Scales - modified (KFLS-M)* is a four-item questionnaire based on the original KFLS administered to parents, designed to assess the parent-perceived level of satisfaction in the relationships with the other family members [26]. *The Experiences in Close Relationships - short form (ECR-S)* is a 12-item questionnaire designed to measure attachment styles in adults, particularly avoidant and anxious attachment styles. The measure is based upon the 36-item Experiences in Close Relationships. In the current study, it will be used to measure attachment styles of both parents. *The BEST Parenting Questionnaire* is a purpose designed, 15-item questionnaire designed to assess parenting experiences, comprising of two subscales that signify emotional dependence on adolescent behavior and assertive parenting. The items were developed to assess changes in behaviors emphasized within the BEST program curriculum [22].

